## Abstract

**Background:** Early life nutrition may affect individuals’ susceptibility to adult non-communicable diseases (NCD). Psychological stress is a well-recognised NCD risk factor. Recent evidence suggests that impaired foetal nutrition alters neuro-endocrine pathways, and hypothalamic-pituitary-adrenal axis feedback systems, resulting in abnormal stress responses, and NCD risk. This study aims to examine adolescent cortisol and cardiovascular stress responses in relation to maternal nutrition and contemporaneous NCD risk markers.

**Methods**: The study sample will be drawn from three well-established birth cohorts in India; the Parthenon cohort, Mysore (N=550, age~20y), the SARAS KIDS prenatal intervention cohort, Mumbai (N=300, age~10-12y) and the Pune Rural Intervention in Young Adults/ PRIYA cohort, Pune (N=100, age~22y). We will perform the ‘Trier Social Stress Test (TSST)’, a well-accepted stress-test module which involves participants performing 5-minutes each of public speaking and mental arithmetic tasks in front of unfamiliar ‘judges’ (stressor). Repeated measures of salivary cortisol and autonomic cardiovascular outcomes relative to the stressor will be assessed. Measures of psychological stress, cognitive function, blood pressure, glucose-insulin metabolism and depression will be carried out. Mechanistic studies including DNA methylation in gluco-corticoid receptor (
*NR3C1*) and
*11β-HSD2* gene loci and neuroimaging will be carried out in a subsample. Qualitative interviews and focus group discussions in a subsample of the Parthenon cohort will explore the perception of stress and stressors among the youth.

We will convert repeated measures into time-weighted averages before analysis. We will carry out multivariable regression analysis to test the associations. We will further refine the analyses using the mixed-model regression and conditional analyses for the association with repeated measures.

**Ethics and dissemination:** This study has been approved by the research ethics committee of CSI Holdsworth Memorial Hospital, Mysore. The findings will be disseminated locally and at international meetings, and reports will be submitted to open access peer reviewed journals.

## Introduction

Psychological stress is an unpleasant subjective experience, caused by an awareness of situational demands exceeding an individual’s adaptive capacity
^1^. It has been identified as an important lifestyle risk factor for adult non-communicable disease (NCD)
^2^. During stress, the body triggers physiological changes through the actions of the hypothalamic-pituitary-adrenal (HPA) axis (and its end product cortisol) and the autonomic nervous system, to maintain homeostasis
^2^. It is suggested that repeated psychological stress induces dysregulated HPA axis activity and autonomic cardiovascular control, reflected in either exaggerated or blunted responses of these systems to acute stress. Over time, these abnormalities can provoke the cardiometabolic, neuroendocrine and immunological disorders responsible for NCDs. Studies have shown increased cardiovascular and mental health disorders in relation to abnormal stress responses
^3,
4^.

The “Developmental Origins of Health and Disease (DOHaD) hypothesis” proposes that variations in nutrition during foetal development influence individual’s susceptibility to adult NCDs
^5^. Both intra-uterine growth restriction (resulting in low birthweight), and accelerated growth caused by maternal gestational diabetes (GDM), increase the risk of NCDs
^6–
8^. This phenomenon is thought to reflect permanent effects (‘programming’) of unbalanced foetal nutrition on physiological systems
^9^. Recent evidence suggests that altered neuro-endocrine responses to stress may be a pathway linking early life nutrition to the development of NCDs in later life
^10^. Maternal nutrients, particularly those involved in the one-carbon metabolism are vital for many neuro-developmental processes, and their deficiencies may alter neuroendocrine structure and function
^11,
12^, impair HPA axis feedback systems
^13,
14^, and influence stress reactivity. A few studies in adults and children have found associations between lower birth weight (as a proxy for maternal undernutrition) and higher cortisol and cardio-sympathetic responses to stress
^15–
18^. However, relationships of maternal nutritional status and maternal hyperglycemia
*per se* with offspring stress responses are not known.

There is an escalating prevalence of NCDs in India; ~80 million people in the country are expected to develop type 2 diabetes by 2030
^19^, and the estimated prevalence of GDM is ~15% currently
^20^. With recent socio-economic transition, resulting in energy dense diets and physical inactivity, these conditions are increasingly affecting younger age groups
^21^. Recent reports suggest that stress levels are also increasing steadily among youth, resulting in a growing prevalence of anxiety disorders, depression and suicide
^22,
23^. In India, widespread maternal undernutrition, with specific micronutrient deficiencies, as well as high rates of maternal GDM, may confer long-term cardiometabolic and neuro-cognitive adverse effects on the offspring
^24^. However, there is limited evidence for the early life programming of stress responses as a risk factor for NCDs in India. Our own studies at Holdsworth Memorial Hospital (HMH), Mysore showed that increased HPA axis activity, measured using fasting plasma cortisol concentration, was associated with higher cardiometabolic risk markers in adults and children
^25,
26^. Subsequently we observed that the adolescent offspring of GDM mothers (OGDM) exhibited exaggerated cardiovascular responses to acute stress
^27^.

Adolescence, the developmental period from the onset of puberty until the attainment of social independence, is associated with intense negative emotions, stress perception and reactivity
^28^. These attributes are thought to result from extensive re-modelling of cortical brain structure and changing efficiency of cognitive and emotional control occurring during this period
^28^. Stress-related behavioural and physiological changes during adolescence and early adulthood may initiate risk trajectories for NCDs, and may also have adverse implications for future offspring through programming effects, thus perpetuating the risk cycle. Various biological, environmental and social factors may determine variations in stress-reactivity
^29^. Understanding these factors, critical life course periods during which they influence changes in stress responses, and mechanisms underlying these changes may lead to interventions to mitigate their adverse effects on health. The current study proposes to build on the previous evidence to understand the life course factors that predict adolescent stress responses.

## Aims and objectives

The overarching aim of the study is to understand modifiable factors that might reduce stress responses and guide the development of an integrated intervention to reduce stress reactivity, and therefore future risk of NCDs in adolescents and young adults in India.

The key objectives are to:

1. Test the persistence of the association of birth weight, and maternal GDM and micronutrient status with cortisol and autonomic cardiovascular responses to acute stress in adolescents2. Examine the association of stress responses with their psychological and cardiovascular risk markers3. Test the role of prenatal nutritional intervention in reducing physiological stress responses in the adolescent offspring4. Test whether nutritional supplementation during adolescence/young adulthood is associated with improved stress responses in young adults exposed to maternal nutritional deficiency5. Investigate specific epigenetic (methylation) changes, and neurocognitive characteristics that relate to stress responses, and6. Develop a socio-cognitive intervention model to be used in a future study to reduce stress responses in adolescents and young adults

## Protocol

### Study sample

The “Stress Responses in Adolescence and Vulnerability to Adult Non-communicable disease (SRAVANA) study” will adopt a multi-centric approach, leveraging on the unique characteristics of three Indian birth cohorts to achieve specific, but complementary objectives.

**The Mysore Parthenon Cohort** was established at HMH in 1997–1998 to investigate the long-term effects of maternal GDM and nutritional status on offspring NCD risk
^30^. The cohort comprised 663 normal offspring of 830 women whose GDM status had been assessed; ≈6% of them were OGDM
^31^. Offspring follow-up continued every 6–12 months after birth for anthropometry, body composition, pubertal staging, cardiometabolic and cognitive assessments. The study showed high rates of low maternal B12 and vitamin D status, and GDM, suggesting that undernutrition and overnutrition co-exist in this transitioning population
^31–
33^. Offspring exposed to maternal GDM had greater adiposity, insulin resistance and systolic BP, and higher cardiovascular stress responses during adolescence than those of mothers with normal glucose tolerance
^27,
34^. Higher risk markers were also observed in relation to lower offspring birthweight and maternal nutritional imbalances (vitamin D, folate and homocysteine)
^32,
33,
35^.

The cohort participants are currently aged 20, and ≈85% of the original cohort are still being followed up (N=550). For the present study, we will measure NCD risk markers, chronic stress in the whole cohort, and acute stress responses in a subsample (N~250) who participated in earlier studies of stress reactivity at the age of 13.5 years
^27^. See below for a detailed description of these assessments.

**The Mumbai Maternal Nutrition Project** (MMNP or “Project SARAS”; ISRCTN 62811278) was a community-based randomised trial of nutritional supplementation for women living in urban slums, pre-conceptionally and throughout pregnancy
^36^. The primary outcome was birth weight, but the study was designed to have enough power to study long-term effects on body composition, cardiometabolic risk markers and cognitive function in the children. The intervention was a daily snack (such as samosas and fritters) made from micronutrient-rich foods (milk, green leafy vegetables and fruit). Women in the control group received a similar snack made from foods of lower micronutrient content such as potato and onion. A total of 6513 women were randomised, 2291 women became pregnant, and 1962 delivered live singleton newborns during 2006–2012. The study showed that supplementation increased offspring birthweight among women of normal or high body mass index
^36^. The incidence of GDM was halved in the intervention mothers compared to controls
^37^.

SARAS KIDS is the ongoing follow-up study of the offspring born to these women. In the SRAVANA study, we will randomly select 150 offspring each from the maternal intervention and control groups and all available OGDM during early adolescence (~10–12y). We will measure NCD risk markers and stress responses. We will test the hypothesis that ‘prenatal nutritional supplementation normalises cortisol and cardiovascular stress responses, especially in OGDM’.

**The Pune Maternal Nutrition Study (PMNS)** was a community based observational study set up in rural Pune in 1993
^38^. Non-pregnant, married women were identified, and followed up until they became pregnant (N=797). Pregnant women were assessed for diet, micronutrient status and foetal growth. The 753 offspring formed the PMNS cohort, and had detailed anthropometry at birth and at 6-monthly intervals. Maternal undernutrition (low BMI and vitamin B12 status) was widespread in this population. Low B12 status in the mothers was associated with higher insulin resistance in the children.

The PMNS offspring are now part of a community-based intervention study (ISRCTN 32921044), with the hypothesis that physiological doses of micronutrient supplementation during adolescence/young adulthood will improve the birthweight, B12 status, and newborn and childhood body composition in the next generation
^39^. The cohort members (N=557) were enrolled when they were ~16–18y old, and were randomised to receive either i) B12 2µg, ii) B12 2µg plus multiple micronutrients plus milk protein (MMN), or iii) placebo daily. The intervention is ongoing. We will recruit ~50 participants each from the intervention and placebo groups at 22–23y of age. We will measure NCD risk markers and stress responses. We will test the hypothesis that current micronutrient supplementation is associated with improved cortisol and cardiovascular responses to stress in young adults exposed to maternal nutritional deficiencies.

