## Conclusion

Altered neuro-endocrine reactivity to stressful situations is a risk factor for cardiovascular and mental health disorders in humans. Previous studies in India and other parts of the world have shown consistent associations between impaired early life nutrition and increased risk of these disorders. There is limited evidence for a role of early nutritional programming of stress responses, though this is considered one of the pathways for increased adult disease risk. Micronutrient deficiencies, especially of one-carbon nutrients, are associated with psychological manifestations of stress in humans
^58^. However, there are no studies examining the effect of nutritional supplementation on physiological stress responses in young individuals. Our study attempts to fill gaps in this area of research and explore in detail behavioural, environmental, epigenetic and neurological aspects linking early nutritional exposure to variations in stress reactivity.

To our knowledge, this is the first study to explore the role of life course nutrition on adolescent stress responses in humans. The study will generate robust evidence for the role of intra-uterine nutritional imbalances in the development of NCDs through programming of abnormal stress responses. Capitalising on the existing intervention designs in two well-known Indian birth cohorts, it will determine whether 1) prenatal nutritional supplementation and 2) current nutritional supplementation mitigates abnormal stress responses in vulnerable adolescents. The secondary analysis of these data, along with the existing past data, will guide the development of multi-faceted interventions for reducing NCD risks through a life course approach.

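### The Mumbai hypothesis singles out offspring of mothers with gestational diabetes (OGDM), a group formed after randomisation and halved by the intervention, so that part of it has no randomised test

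*Protocol article*

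**What the plan says.** All of the relevant text is in the Study sample section of the protocol article, under the Mumbai Maternal Nutrition Project.

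- **Design.** The parent study was a "community-based randomised trial of nutritional supplementation for women living in urban slums, pre-conceptionally and throughout pregnancy".
- **Effect on GDM.** "The incidence of GDM was halved in the intervention mothers compared to controls".
- **Sampling.** The present study will "randomly select 150 offspring each from the maternal intervention and control groups and all available OGDM during early adolescence". The number of OGDM is not stated. The Abstract gives 300 for Mumbai, which is the two random groups alone.
- **Hypothesis.** "prenatal nutritional supplementation normalises cortisol and cardiovascular stress responses, especially in OGDM".

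Elsewhere, objective 3 (Aims and objectives) concerns the role of the prenatal intervention and does not mention OGDM. The sample size section gives one detectable arm difference for Mumbai, 0.23 SD, for whole arms. The Data analysis section plans covariate-adjusted regression and mixed models. Nothing in the article identifies GDM as a post-randomisation variable or marks the OGDM comparison as non-randomised.

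**The concern.** Randomisation balances the arms among all women allocated. It does not balance them within a group whose membership the allocation has changed. If the snack prevented about half of GDM, the two arms' OGDM groups come from different sets of mothers. Any characteristic that influences both the tendency to GDM and the child's stress response can then produce an arm difference with no effect of the snack, or hide a real one.

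There is a second problem. The article reports higher cardiovascular stress responses in adolescents exposed to maternal GDM (Mysore) and a halving of GDM under supplementation (Mumbai). Preventing GDM is thus a plausible route by which the snack could help. A child whose mother was spared GDM is not in the OGDM group, so a contrast within OGDM cannot count that benefit.

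What is at stake is the part of the hypothesis that says the effect is stronger in OGDM. A reader would take it as a finding from a randomised trial.

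**Working it through.** **Plan's own figure.** None is given for an OGDM contrast. The nearest is the whole-arm 0.23 SD. With 150 per arm, two-sided 5% and 80% power (stated for Mysore, assumed here), the detectable difference is 2.80 × √(2/150) = 0.32 SD; 0.23 equals 2.80/√150. That is a separate matter, and nothing below depends on it.

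**Step 1: order of events.** Allocation and supplementation come before conception, GDM arises in pregnancy, and the incidence ratio is about 0.5. Both premises are in the Study sample section. It follows without further figures that OGDM status is a consequence of allocation.

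**Step 2: illustration of the selection.** Assumptions, none of them from the Mumbai data:

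- GDM occurs when a standard normal liability L exceeds a threshold.
- The control GDM rate p is 6% (the OGDM share in the Mysore cohort) to 15% (the national estimate in the Introduction).
- The snack moves the threshold so that the rate becomes p/2.
- The snack has no effect on the stress outcome.
- The outcome, in SD units, has correlation ρ with L.

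The mean liability of cases is E(p) = φ(z_p)/p, where z_p is the upper-p normal quantile. The spurious difference within OGDM (intervention minus control) is ρ × [E(p/2) − E(p)].

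| p | E(p) | E(p/2) | Difference | ρ = 0.1 | ρ = 0.3 | ρ = 0.5 |
|---|---|---|---|---|---|---|
| 6% | 1.985 | 2.268 | 0.283 | 0.03 | 0.08 | 0.14 |
| 10% | 1.755 | 2.063 | 0.308 | 0.03 | 0.09 | 0.15 |
| 15% | 1.554 | 1.887 | 0.333 | 0.03 | 0.10 | 0.17 |

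**Step 3: the interaction.** Offspring not exposed to GDM are selected too, since the prevented cases sit there in the intervention arm only. Their mean liability is −E(p) × p/(1 − p). At p = 6% this is −0.127 in controls and −0.070 in the intervention arm, a difference of 0.057. The spurious interaction is then ρ × (0.283 − 0.057) = 0.02 to 0.11 SD for ρ 0.1 to 0.5. At p = 15% it is ρ × (0.333 − 0.121) = 0.02 to 0.11 SD. In the whole arms the mean liability is zero on both sides, so the whole-arm contrast is unbiased in this model.

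**Step 4: adding all available OGDM.** Take equal arms of 1962/2 = 981 births and full follow-up, which is an upper bound.

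- At p = 6% there are 59 control and 29 intervention OGDM. The random 150s would already hold about 9 and 4.5, so about 50 and 25 would be added. OGDM would form 59/200 = 29% of the control sample and 29/175 = 17% of the intervention sample, against 6% and 3% in the source arms.
- At p = 15% the shares are 147/275 = 54% and 74/212 = 35%, against 15% and 7.5%.

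An unweighted whole-arm comparison that includes the added children would therefore compare arms of different make-up. Part of that difference comes from the sampling and not from the snack.

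**The case against.** The strongest reply is that the article states a hypothesis, not an analysis. The Data analysis section specifies no within-OGDM arm comparison and no arm-by-GDM interaction, and such detail may sit in a fuller document. That is fair as to method. But the hypothesis and the sampling are fixed here, and no analysis plan can turn a contrast within a treatment-altered subgroup into a randomised one. Covariate adjustment helps only for measured common causes of GDM and stress response.

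Several stronger readings are tempting, and the documents do not support them.

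- A reader might infer that the whole Mumbai hypothesis could be decided by selection. It could not. The OGDM clause is a rider; objective 3 and the sample size section concern whole arms, which the random 150 + 150 can test.
- A reader might infer that the Conclusion makes a causal OGDM claim when it asks whether supplementation "mitigates abnormal stress responses in vulnerable adolescents". That phrase covers the Mumbai and Pune interventions together and does not name OGDM.
- A reader might infer that selection would create false support. In the model above with positive ρ, the remaining intervention cases have the higher responses, so the bias runs against the hypothesis. False support needs the opposite sign, and the document settles neither.
- A reader might count the absence of a power figure for OGDM as a fault. A condensed article may leave that out.

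One might also object that every offspring comparison is conditional on conception and live birth ("A total of 6513 women were randomised, 2291 women became pregnant, and 1962 delivered live singleton newborns"). That is true, but the article reports an effect of treatment on GDM and none on conception, so the point is not extended that far. Finally, recruiting all OGDM is sound for objective 1, the association of maternal GDM with stress responses.

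**Conclusion.** The point holds for the OGDM clause and for nothing wider. The structural conclusion rests only on two statements in the article: supplementation preceded GDM and halved it. An arm contrast within OGDM, or an arm-by-GDM interaction, is a non-randomised comparison and omits benefit that acts through preventing GDM.

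The size and sign of the bias cannot be derived from the document. The 0.03-0.17 SD is an illustration that depends on an assumed control GDM rate of 6-15%, an assumed correlation of 0.1-0.5 and the threshold model. It should not be quoted as an estimate. The main clause, the effect of supplementation in the whole arms, keeps its randomised basis if the added OGDM are kept out of that estimate.

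**What to change.** In the Mumbai paragraph of Study sample:

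1. State the randomised hypothesis as the effect of arm on stress responses, estimated in the randomly selected 150 + 150 only.
2. Drop the OGDM clause from the causal hypothesis. Alternatively keep it as an exploratory, non-randomised contrast, adjusted for measured common causes of GDM and stress response and reported as such.
3. If effect modification is of interest, use a factor measured before randomisation. Maternal BMI is a candidate, since "The study showed that supplementation increased offspring birthweight among women of normal or high body mass index", but the article does not say when BMI was recorded, so this must be confirmed first.
4. Label any analysis of GDM as a mediator as observational. It needs the absence of unmeasured common causes and is not protected by randomisation either.

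This is rewording and needs no new data. The sponsor gives up a causal subgroup claim, and the added OGDM do not contribute to the randomised arm estimate, though they still serve objective 1.

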### Assessments (
Table 1)

**The Trier Social Stress Test (TSST)** is a valid method of ethically inducing acute psychological stress, particularly in adolescents
^40^. The test is based on ‘uncontrollability, unpredictability and social evaluative threat (perception of negative assessment of the self by others)’ for inducing stress. We have previously adapted the TSST modified for children (TSST-C) for use in the Parthenon adolescents, and have shown that it is valid for Indian conditions
^41^. The TSST involves participants performing 5-minutes each of public speaking and mental arithmetic tasks in front of unfamiliar evaluators (stressor). Pre-test and post-test saliva samples will be collected for cortisol assessment. Systolic and diastolic blood pressure (BP), cardiac output, stroke volume, heart rate and total peripheral resistance, as measures of autonomic nervous system, will be measured continuously before and during the TSST using a portable hemodynamic monitor (Nexfin, BMEye). Acute stress response will be estimated as the change in post-stress cortisol and cardiovascular parameters from pre-test values (baseline). These measures form the primary outcome of the study.

**Table 1. T1:** List of assessments and outcomes of the proposed study.

Parameters tested	Method	Outcome	Mysore	Mumbai	Pune
**Stress response**	Trier Social Stress Test	Cortisol concentration; continuous blood pressure, heart rate, cardiac output, stroke volume and total peripheral resistance Cortisol and cardiovascular stress response	✓	✓	✓
**Cardiometabolic** **Parameters**	Anthropometry	Weight, height; mid-upper arm, head, waist and hip circumference; subscapular and triceps skinfold	✓	✓	✓
	Body composition (bioimpedance)	Body fat and lean mass	✓	✓	✓
	Hand grip strength (dynamometer)	Muscle strength	✓	✓	✓
	Blood pressure	Resting systolic and diastolic blood pressure; pulse rate	✓	✓	✓
	Oral glucose tolerance test	Diabetes/glucose intolerance	✓	☑	☑
	Fasting blood samples	Fasting insulin for insulin resistance (HOMA-IR); total cholesterol, triglycerides, HDL-cholesterol	✓	☑	☑
**Psychological** **Parameters**	Wechsler’s Adult Intelligence Scale-IV	Cognitive function	✓	☑ *	☑
	PHQ-9	Depression	✓	-	✓
	MINI		✓	-	☑
**Behavioural** **Parameters**	Perceived Stress Scale	Chronic stress	✓	-	✓
	Stressful Life Events Scale		✓	-	✓
	Strengths and Difficulties Questionnaire	Internalising and externalising behaviour	✓	✓	✓
**Lifestyle** **Indicators**	Food Frequency Questionnaire	Dietary intake pattern Nutrient intake quantity	✓	✓	☑
	24-hour Food Recall		✓	✓	✓
	International Physical Activity Questionnaire	Physical activity pattern, intensity and magnitude	✓	✓	✓
	Smoking and Alcohol intake	Addictive behaviour, substance Abuse	✓	-	✓
**Mechanistic** **Assays**	Epigenetic Assay	DNA methylation: *NR3C1, 11β-HSD2*	✓	✓	-
	Magnetic Resonance Imaging for brain	Regional cerebral volumes	✓	✓	☑
**Socio-** **demographic** **Indicators**	Standard of Living Index	Socio-economic Status	✓	✓	✓

✓: SRAVANA study assessments; ☑: Assessed as part of ongoing/recently completed follow-up. HOMA-IR: Homeostasis Model Assessment for Insulin Resistance; MINI: Mini International Neuropsychiatric Interview; PHQ-9: Patient Health Questionnaire-9 *Kauffman’s Assessment Battery and additional tests

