### Data analysis

We will summarise repeated measures of cortisol and cardiovascular response to stress in a time weighted average (TWA). Linear and logistic regression models will be used to examine associations of stress responses (TWA) with risk outcomes (eg. blood pressure, depression). These models will be adjusted for age, sex, socio-economic status, and relevant maternal and offspring co-variates.

We will use linear mixed-model regression analysis to examine associations of maternal exposures with repeated measures of cortisol and cardiovascular parameters to account for within-group correlations.

We will use the conditional analysis method
^57^ to examine the change in stress responses from early adolescence to adulthood in Mysore, to explore tracking.

Metanalysis: We will also do metanalyses of data from Mysore, Mumbai and Pune components of the study on the association of stress responses with 1) maternal nutritional status and 2) offspring NCD risk markers.

Qualitative interviews: Transcripts from qualitative interviews and conversations will be subject to thematic analysis, using a standard thematic analysis methodology involving constant comparative methods.

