### Sample size and power calculation

Mysore: The sample size of the Mysore study component is based on the previous stress-responses study carried out during 2011–2013 among the Parthenon cohort participants
^41^. The previous sample size was calculated based on the only available study in children on the association between birth weight and stress response
^15^. We estimated that our sample will have 80% power to detect an effect size of 2.9 nmol cortisol increase per kg increase in birth weight at 5% significance level. In the current study, we aim to follow-up all the children who had participated in the above study. This sample size will have 80% power at the 5% significance level to detect an association of 0.18 SD of a continuous outcome (eg. TWA salivary cortisol) per SD of an exposure (eg. birth weight).

Mumbai: The sample size calculation for the Mumbai component of the study is based on the Mysore sample size. The estimated sample size will be able to detect an association of 0.16 SD of a continuous outcome per SD of a continuous exposure, and will detect a difference in outcome of 0.23 SD between the intervention and the control arms.

Pune: As there are no earlier studies on the effect of current nutritional intervention on stress responses, we based the sample size for this study on the findings from comparison of effect size between the offspring of B12 deficient and normal B12 status mother. The estimated sample size will detect an association of 0.28 SD of a continuous outcome per SD of an exposure. The study will detect a difference of 0.56 SD in the outcome between the control and intervention group.

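### Seven stress-test measures are jointly the primary outcome and none leads, while each cohort is sized for a single outcome

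*Protocol article*

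**What the plan says.** The Trier Social Stress Test (TSST) paragraph under Assessments has two outcome domains. For cortisol: "Pre-test and post-test saliva samples will be collected for cortisol assessment". For the cardiovascular side: "Systolic and diastolic blood pressure (BP), cardiac output, stroke volume, heart rate and total peripheral resistance, as measures of autonomic nervous system". That is one plus six measures. The paragraph defines the response, "Acute stress response will be estimated as the change in post-stress cortisol and cardiovascular parameters from pre-test values (baseline", and closes with "These measures form the primary outcome of the study". A separate Secondary outcomes section follows, so the split into primary and secondary is deliberate.

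The Data analysis section describes the response differently: "We will summarise repeated measures of cortisol and cardiovascular response to stress in a time weighted average (TWA".

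Under Sample size and power calculation, the Mysore paragraph says "This sample size will have 80% power at the 5% significance level to detect an association of 0.18 SD of a continuous outcome" per SD of exposure, and mentions the time-weighted average of salivary cortisol only as an example. The Mumbai and Pune paragraphs give detectable effects for an unnamed continuous outcome, without restating the significance level.

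Under Study sample, the Mumbai hypothesis is that "prenatal nutritional supplementation normalises cortisol and cardiovascular stress responses, especially in OGDM". The Pune hypothesis also names both domains. The Conclusion says of the study that "it will determine whether 1) prenatal nutritional supplementation and 2) current nutritional supplementation mitigates abnormal stress responses in vulnerable adolescents".

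**The concern.** A primary outcome is meant to fix in advance which result answers the question. Here seven results share that role, and nothing says which of them, or how many, must respond for a hypothesis to be supported. The measures need not agree. Cardiac output is the product of stroke volume and heart rate, and at a given pressure peripheral resistance falls as output rises, so supplementation could lower one measure and raise another.

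The two randomised comparisons (objectives 3 and 4) carry most of the weight, because the Conclusion presents them as determinations. If the deciding measure can be settled after the data are seen, the nominal 5% no longer describes the risk of a false claim. If all seven were instead protected equally, the stated power would not hold.

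**Working it through.** **Inputs from the protocol.** Seven measures (Assessments). About 250 TSST participants in Mysore, 150 per arm in Mumbai and about 50 per arm in Pune (Study sample). 5% significance and 80% power, both written for Mysore only. I assume two-sided tests and the same level and power in Mumbai and Pune. The protocol gives no correlations between measures.

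**1. The stated figures.** For one test, the detectable slope in SD per SD is (1.960 + 0.842)/√N:
- Mysore, N = 250: 2.802/15.81 = 0.177 (stated 0.18)
- Mumbai, N = 300: 2.802/17.32 = 0.162 (stated 0.16)
- Pune, N = 100: 2.802/10 = 0.280 (stated 0.28)

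For two arms of n each, the detectable difference is 2.802 × √(2/n):
- Pune, n = 50: 2.802 × 0.200 = 0.560 (stated 0.56)
- Mumbai, n = 150: 2.802 × 0.1155 = 0.32 (stated 0.23)

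All the per-SD figures and the Pune arm difference reproduce as one test at 5%. The Mumbai arm difference does not. Power at 0.23 SD with 150 per arm is about 51%, and 297 per arm would be needed for 80%. The stated value equals 2.802/√150 = 0.229, which lacks the factor √2 for two groups.

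**2. False-positive chance if any one of seven measures at p<0.05 counted.** If independent: 1 − 0.95⁷ = 0.302. With a common correlation ρ, write each test statistic as √ρ·u + √(1−ρ)·e and simulate the chance that at least one exceeds 1.96 in absolute value (1,000,000 draws):

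| ρ | 0 | 0.3 | 0.5 | 0.7 | 0.8 |
|---|---|---|---|---|---|
| Chance | 30% | 27% | 23% | 18% | 15% |

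A model that builds cardiac output from heart rate and stroke volume, and resistance from pressure and output, with assumed correlations among the rest, gives 24% to 25%.

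**3. Protecting all seven equally.** Bonferroni uses 0.05/7 = 0.00714, with critical value 2.690. Power at the stated per-SD effects is then Φ(effect × √N − 2.690):
- Mysore: Φ(2.846 − 2.690) = 56%
- Mumbai: Φ(2.771 − 2.690) = 53%
- Pune: Φ(2.800 − 2.690) = 54%

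**4. Two lead measures.** The first Holm step uses 0.025, so 2.241 + 0.842 = 3.083 replaces 2.802:
- Mysore: 3.083/√250 = 0.195 SD per SD
- Mumbai: 3.083/√300 = 0.178 SD per SD; 3.083 × √(2/150) = 0.356 SD between arms
- Pune: 3.083/√100 = 0.308 SD per SD; 3.083 × √(2/50) = 0.617 SD between arms

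Once one lead measure is significant, Holm tests the other at 5%, so these are the cautious values.

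**The case against.** The strongest reply is that the protocol never says one significant measure is enough. The Mumbai and Pune hypotheses join cortisol with cardiovascular responses, which can be read as requiring both domains, and that reading would not produce the inflation in step 2. This stands: the inflation is conditional on a rule that the protocol leaves open.

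A second reply is that multiplicity procedures belong in an analysis plan or full protocol, neither of which is shown. That also stands, so the lack of an alpha split or testing order is not itself the point. What remains is the article's own choice to designate all seven measures as primary without a lead, next to sizing that assumes one.

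A reader might infer that cortisol is already the sizing outcome and should simply become the sole primary. The text does not support this. Cortisol was the basis of the earlier Mysore study's sizing and is only an example for the present one, and Pune's paragraph names no outcome. The team's own earlier stress-test finding, in offspring of mothers with gestational diabetes, was cardiovascular, so ranking every cardiovascular measure behind cortisol would set aside a well-motivated question.

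**Conclusion.** The primary outcome is badly fixed: seven measures share the role, none leads, and the sizing fits only one. The response metric is also unsettled, since Assessments uses change from baseline and Data analysis uses a time-weighted average.

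Under an any-one-measure rule the false-positive chance per contrast would be about 15% to 30%, three to six times 5%. That rests on seven two-sided 5% tests and a common correlation between 0.8 and 0.

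Two stronger readings go too far. One is a single rate, such as 23% for every cohort: it needs a correlation of 0.5 that the documents do not give and a decision rule that they do not state. The other is a much higher overall rate for Mysore, obtained by multiplying measures by exposures: the objectives do not say how many micronutrients will be tested, so that count would be invented.

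**What to change.** Make these changes before Mumbai and Pune stress data exist. At the time of the article, ethical permission at both sites was still to be sought, and 82 Mysore participants had completed the test.

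- **Assessments:** name one lead cortisol measure and one lead cardiovascular measure (for example systolic BP), matching the two domains in the hypotheses. Label the other five measures secondary.
- **Assessments and Data analysis:** reconcile change from baseline with the time-weighted average, and use one metric in both.
- **Study sample:** name the deciding contrast in each cohort. For Pune, say which of the two active arms, or both, form the intervention group.
- **Testing:** apply Holm to the two lead measures at 5% within each contrast.
- **Sample size:** restate detectable effects at 80% power and alpha 0.025 as about 0.20 SD per SD (Mysore); 0.18 SD per SD and 0.36 SD between arms (Mumbai); 0.31 SD per SD and 0.62 SD between arms (Pune). If a single lead measure is preferred, the per-SD figures and Pune's 0.56 SD stand, but Mumbai's between-arm figure must become 0.32 SD, not 0.23.
- **Conclusion:** limit the promise to determine supplementation effects to the lead measures.

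The cost is wording only, with no extra participants or assays. Detectable effects become slightly less favourable, and an isolated result on another haemodynamic measure can no longer carry the main claim.
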